# Targeted full energy and protein delivery in critically ill patients: a study protocol for a pilot randomised control trial (FEED Trial)

**DOI:** 10.1186/s40814-018-0249-9

**Published:** 2018-02-20

**Keywords:** Nutritional support, Enteral nutrition, Nutritional requirements, Dietary protein, Critical illness, Critical care, Intensive care

## Abstract

**Background:**

Current guidelines for the provision of protein for critically ill patients are based on incomplete evidence, due to limited data from randomised controlled trials. The present pilot randomised controlled trial is part of a program of work to expand knowledge about the clinical effects of protein delivery to critically ill patients. The primary aim of this pilot study is to determine whether an enteral feeding protocol using a volume target, with additional protein supplementation, delivers a greater amount of protein and energy to mechanically ventilated critically ill patients than a standard nutrition protocol. The secondary aims are to evaluate the potential effects of this feeding strategy on muscle mass and other patient-centred outcomes.

**Methods:**

This prospective, single-centred, pilot, randomised control trial will include 60 participants who are mechanically ventilated and can be enterally fed. Following informed consent, the participants receiving enteral nutrition in the intensive care unit (ICU) will be allocated using a randomisation algorithm in a 1:1 ratio to the intervention (high-protein daily volume-based feeding protocol, providing 25 kcal/kg and 1.5 g/kg protein) or standard care (hourly rate-based feeding protocol providing 25 kcal/kg and 1 g/kg protein). The co-primary outcomes are the average daily protein and energy delivered to the end of day 15 following randomisation. The secondary outcomes include change in quadriceps muscle layer thickness (QMLT) from baseline (prior to randomisation) to ICU discharge and other nutritional and patient-centred outcomes.

**Discussion:**

This trial aims to examine whether a volume-based feeding protocol with supplemental protein increases protein and energy delivery. The potential effect of such increases on muscle mass loss will be explored. These outcomes will assist in formulating larger randomised control trials to assess mortality and morbidity.

**Trial registration:**

Australian New Zealand Clinical Trials Registry (ANZCTR), ACTRN: 12615000876594 UTN: U1111-1172-8563.

## Background

Nutritional therapy, preferably via the enteral route, is part of the standard care for critically ill patients [1]. Prominent critical care nutrition guidelines recommend that protein should be provided at a level of 1.2–2.0 g/kg/day, with possibly higher amounts for patients with multi-trauma, obesity and burns and greater than 80% of energy targets should be met [1]; however, there is a lack of high-quality evidence to support these guidelines [2]. Despite these and similar guidelines, nutritional delivery in the intensive care unit (ICU) is frequently less than these targets; observational data from a large international dataset suggests that critically ill patients only receive, mean SD, 43 g ± 27 of protein and 1054 kcal ± 717 of energy per day, which equates to approximately 50 and 60% of their protein and energy targets, respectively [3]. More recent observational data from this dataset suggests that increasing protein delivery by 30 g, or meeting greater than 80% of prescribed protein targets, is associated with greater survival, an increase in ventilator-free days and a shorter time to discharge alive from the ICU [4, 5]. In addition, data from a prospective observational cohort study from a single centre suggested that the provision of more protein (greater than 1.5 g/kg/day) was associated with a reduction in mortality when adjusted for severity of illness and age [6]. Finally, observational study and preliminary trial data supporting the concept that increasing calorie delivery will improve outcomes [7–9].

Standard enteral feeding regimens are generally based on an hourly target rate of administration of a selected formulation, calculated according to daily energy and protein targets [10]. Therefore, if interruptions to feed delivery occur, protein and energy targets are not met [11]. Furthermore, protein delivery is generally restricted by the composition of the enteral formula available because overall energy requirements mostly determine the volume of the formula prescribed. In a cluster randomised control trial, Heyland and colleagues reported that with a novel approach to feeding, including a volume-based feeding protocol, delivery of protein increased by 14% (95% CI, 5–23%) and calories by 12% (95% CI, 5–20%) [11]. However, theoretically, volume-based feeding protocols with protein supplementation may not achieve greater delivery of protein and energy to patients due to issues with feeding intolerance, as increased nutrient delivery, particularly protein, to the small intestine, stimulates the feedback loop to slow gastric emptying [12, 13]. Therefore, this approach may inadvertently decrease protein and energy delivery.

Beyond mortality, patient-centred functional outcomes in survivors of critical illness are increasingly being recognised as important variables that may be influenced by nutrition [14, 15]. This includes muscle weakness, which is often described as Intensive Care Unit Acquired Weakness (ICUAW) [16]. Lower health-related quality of life (HRQoL) scores are associated with ICUAW, emphasising that weakness is important to patients [17–19]. The loss of skeletal muscle has been identified as a crucial contributing factor to the development of ICUAW [20, 21], with ultrasound being a potentially useful and minimally invasive modality to quantify muscle mass and muscle loss in the critically ill [22–24].

Augmenting nutrient delivery, particularly increased protein delivery, has been proposed as an approach that may attenuate muscle loss associated with critical illness. At present, there is an absence of robust data to support this approach [25] and recent studies have reported conflicting conclusions [6]. Most recently, Ferrie and colleagues [26] performed a randomised controlled trial in parenterally fed patients. Amongst other outcomes, they measured muscle mass and strength [26]. This study of 119 critically ill patients, who were randomised to receive a target of either 0.8 or 1.2 g/kg protein per day with isocaloric parenteral nutrition, did not find strong evidence of a difference in the primary outcome of handgrip strength at day 7, but the observed point estimate was in the direction of benefit for those receiving greater protein delivery. Moreover, the augmented protein intervention may have been associated with reduced fatigue and greater forearm muscle thickness using ultrasound [26]. A retrospective observational study of 106 critically ill patients, by Ishibashi and colleagues, reported that protein intake above 1.5 g/kg/day substantially reduced total body protein loss when compared to those who receive less than 1.1 g/kg/day [27]. In contrast, Casaer and colleagues reported that greater calorie and protein administration, particularly when delivered via the parenteral route, reduced the quantity and quality of muscle and was associated with greater muscle weakness [28]. This negative signal was also described by Puthucheary and colleagues, who reported greater muscle wasting associated with increased protein delivery [29].

At present, there is conflicting evidence around the optimal protein provision to critically ill patients including a lack of high-quality evidence which includes patient-centred functional outcomes. This single-centre pilot trial in mechanically ventilated critically ill patients is part of a program to explore the influence of protein prescription on outcomes; aims to determine whether a volume-based enteral feeding protocol with additional protein supplementation delivers a greater amount of protein and energy than a standard nutrition protocol.

## Study objectives

### Co-primary

The primary aim of this pilot study is to determine whether a volume-based feeding protocol with supplemental protein potentially improves the average daily protein and energy delivery, when compared to standard care in mechanically ventilated critically ill patients.

### Secondary

The secondary aims are to evaluate whether a volume-based feeding protocol with supplemental protein when compared to standard care:I.Improves overall protein and energy adequacy without increasing feeding intolerance or diarrhoea.II.Improves nutritional-related outcomes including the incidence of malnutrition at ICU discharge or mid upper arm circumference change from baseline to discharge.III.Decreases the change in quadriceps muscle layer thickness (QMLT) from baseline to ICU discharge.IV.Decreases the incidence of ICUAW or alters muscle strength or physical function scores at ICU discharge.V.Alters the duration of the ICU admission, number of deaths, and the requirement for discharge to a rehabilitation facility.

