### Baseline data collection

Baseline measurements will reflect the status of patients at or prior to randomisation. Demographic data includes admission diagnosis, comorbid illness including quantification using the Charlson Comorbidity Index [32], Katz Activities of Daily Living (ADL) index [33] (prior to the ICU admission), Acute Physiology and Chronic Health Evaluation II (APACHE II) score, and admission Sequential Organ Failure Assessment (SOFA) Score. Baseline measures, collected by the study Dietitian, include height (using ulna length [34]), weight (from bed scales), body mass index (BMI), mid upper arm circumference, nutritional status using the subjective global assessment (SGA) [35, 36], plasma albumin, highest and lowest blood glucose in the first 24 h of ICU admission, independent dietitian estimation of energy (weight-based or Schofield equation [37]) and protein requirements and the first quadriceps muscle layer thickness measure [24], see Table 3 for details of data collection.

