The other secondary outcomes are total calorie and protein provision, calorie deficit and protein adequacy, incidence of feed intolerance, number of days of feed intolerance, incidence of diarrhoea defined as more than three bowel actions or greater than 300 ml per day [43], length of ICU stay, hospital mortality at 28 and 60 days, discharge destination, muscle strength, the incidence of ICU AW and physical function at ICU discharge, and the change in nutritional markers over the study period. Nutritional markers include assessment of malnutrition using the Subjective Globe Assessment (SGA) [35], mid upper arm circumference (MUAC), and body weight. These measures will be carried out at baseline, day 5, and at discharge from ICU; the change from baseline to discharge or day 15 will be calculated. The presence of acute renal failure defined by the RIFLE criteria [44] and plasma urea and creatinine levels will be assessed on a daily basis.

Protein adequacy will be determined over the ICU admission or until day 15 by adding the daily protein provision and comparing this to the estimated protein requirements determined by the dietitian. The protein adequacy will then be explored in relation to the other outcome measures.

Calorie deficit will be determined using both predicted weight-based energy requirements (25 kcal/kg). In eligible patients, calorie deficit will also be calculated using measured energy expenditure (MEE) [45]. Cumulative calorie deficit will be calculated over the ICU admission or until day 15 of the study. MEE will be assessed with indirect calorimetry using E-sCOVX (GE, Helsinki, Finland) [46]. The first MEE will be within 24 h of enrolment into the study and repeated on day 3, day 5, and day 7 of the ICU stay. The measurements will be carried out with the patient in a fed state lying supine. The measure will be taken over a 2-h period, and the summary data of respiratory quotient (RQ) and MEE will be recorded. The feeding rates will not be adjusted in relation to the MEE [47]. Contraindications to carrying out a metabolic measurement will include if the patient is on continuous renal replacement therapy or extracorporeal membrane oxygenation (ECMO) or if the patient has an intercostal catheter with an air leak or is on a fraction of inspired oxygen greater than 0.6 [47].

Feed intolerance will be determined as a single gastric residual volume > 300 ml [48].

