### Statistical analysis

All analyses will use an intention-to-treat approach. Baseline patient demographics, severity of illness, ICU length of stay, mortality, and nutritional markers will be tabulated according to the treatment group. Initial exploratory data analysis will involve calculation of summary statistics and comparison between treatment groups using non-parametric (Wilcoxon), parametric (*t* test), and Fisher’s exact tests as appropriate, as well as construction of trajectory plots according to the treatment group. The co-primary outcomes of average daily energy and protein delivery will be compared between treatment and control groups with two-sample unpaired *t* tests, with statistical significance for each set conservatively at two-sided values of 0.025 to limit the family-wise type 1 error for the two co-primary outcomes to less than 0.05 overall.

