All secondary outcomes will be regarded as exploratory and hypothesis-generating, with no multiple comparison adjustment to conventional 5% type 1 error thresholds. Group differences for change from baseline at selected time points in continuous outcome variables, including QMLT, will be compared after adjustment for initial values using analysis of covariance (ANCOVA) regression models, initially unadjusted, and subsequently adjusted as described below for other regression models. Natural logarithmic transformations may be applied to stabilise variance within these or other linear models if appropriate. The relationships between calorie deficits using both prescribed calories (25 kcal/kg) and MEE and protein adequacy and the outcome measures (QMLT change, muscle strength, diagnosis of ICUAW, and physical function at ICU discharge) will be explored using linear or logistic regression analyses, with adjustment for likely confounders and any baseline variable found to show substantial imbalance between treatment groups. Finally, a population-averaged generalised linear model using a generalised estimating equation (GEE) approach with an unstructured working correlation matrix and robust standard error estimates adjusted for clustering within individual subjects will be applied to these longitudinal data to evaluate the overall associations of the vector of (untransformed or log transformed) outcome variables with treatment group across multiple time points. Multiple imputations for missing data may be used to support conclusions from other generalised linear models constructed without imputation of missing data. Data analysis will be carried out using the Statistical Package for the Social Sciences (SPSS) (IBM® SPSS® Statistics Premium Grad Pack Version 22.0) or Stata Corporation (Stata Statistical Software: Release 15. College Station, TX: StataCorp LP; 2017).

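### Secondary aim II does not settle whether patients malnourished at baseline count as cases, and the group comparison stated for this binary outcome does not use the baseline SGA already collected

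*Protocol article*

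**What the plan says.** All references are to the protocol article.

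- **Study objectives, Secondary, aim II:** "Improves nutritional-related outcomes including the incidence of malnutrition at ICU discharge or mid upper arm circumference change from baseline to discharge".
- **Secondary outcomes:** the list includes "the change in nutritional markers over the study period". SGA is one of these markers. It is taken at baseline, day 5 and ICU discharge, and a change from baseline to discharge or day 15 is to be calculated.
- **Baseline data collection:** SGA is recorded at or before randomisation.
- **Table 1:** no criterion excludes patients who are malnourished at entry.
- **Statistical analysis, group comparisons:** the initial exploratory step is "comparison between treatment groups using non-parametric (Wilcoxon), parametric (*t* test), and Fisher’s exact tests as appropriate".
- **Statistical analysis, baseline adjustment:** "Group differences for change from baseline at selected time points in continuous outcome variables, including QMLT, will be compared after adjustment for initial values". This is the ANCOVA rule.
- **Statistical analysis, other models:** the adjusted linear and logistic regressions relate calorie deficit and protein adequacy to QMLT change, strength, ICUAW and physical function. Malnutrition is not among those outcomes. A GEE model for treatment group over time is also planned, with no stated term for baseline malnutrition.
- **Status:** all secondary outcomes are exploratory and tested at 5% without multiplicity adjustment.

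**The concern.** Within one sentence, aim II ties arm circumference to baseline but gives malnutrition only a time point. The Secondary outcomes section ties SGA to baseline and allows a different end point (discharge or day 15). A reader therefore cannot tell which of two questions is meant: how many patients are malnourished at the end, or how many became malnourished.

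The difference matters because patients malnourished at entry can be enrolled. If end status is compared without regard to entry status, patients whose status was set before randomisation sit in both numerators. They can attenuate the contrast and add noise. With simple randomisation of 60 patients, a chance difference in baseline malnutrition also passes into the discharge comparison. The Discussion in the abstract says the outcomes are to help formulate larger trials, so a prevalence reported as an incidence could mislead planning on both event rate and effect.

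**Working it through.** **1. The plan's own figure.** There is none to reproduce. The Sample size section covers protein intake and QMLT only, and no malnutrition rate appears anywhere. Every rate below is assumed.

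**2. The wordings side by side.**

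| Place | What is measured | End point | Who is at risk |
|---|---|---|---|
| Aim II | incidence of malnutrition | ICU discharge | not stated |
| Secondary outcomes | change in SGA from baseline | discharge or day 15 | not stated |

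The word *incidence* does not decide the matter. Aim IV uses it for ICUAW, which the Secondary outcomes section defines as an MRC sum score below 48/60. That is status against a threshold: strength is first tested at awakening, and no pre-randomisation score is described.

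**3. Which stated analysis reaches a binary malnutrition outcome.** ANCOVA does not (continuous outcomes only). The adjusted regressions do not (different exposures, malnutrition not listed). The GEE might, but the text does not say so and states no baseline malnutrition term. Fisher's exact test fits, and it takes no covariate.

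**4. Attenuation if end status is compared.** Let *f* be baseline prevalence, *p* the rate of new malnutrition among the rest, and *r* the recovery rate among baseline cases. With subscripts c for control and t for intervention:

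- End prevalence in an arm = f(1 − r) + (1 − f)p
- Control minus intervention = f(r_t − r_c) + (1 − f)(p_c − p_t)

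If baseline cases persist, or recover equally in both arms, the first term is zero and the risk difference is multiplied by (1 − f). Assume p_c = 0.40, p_t = 0.20 and no recovery:

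| f | Control | Intervention | Difference | Ratio |
|---|---|---|---|---|
| 0 | 0.40 | 0.20 | 0.20 | 0.50 |
| 0.20 | 0.20 + 0.80 × 0.40 = 0.52 | 0.20 + 0.80 × 0.20 = 0.36 | 0.16 | 0.69 |
| 0.30 | 0.30 + 0.70 × 0.40 = 0.58 | 0.30 + 0.70 × 0.20 = 0.44 | 0.14 | 0.76 |
| 0.40 | 0.40 + 0.60 × 0.40 = 0.64 | 0.40 + 0.60 × 0.20 = 0.52 | 0.12 | 0.81 |

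**5. Chance imbalance.** With about 30 per arm, the standard deviation of the between-arm difference in baseline prevalence is √(2f(1 − f)/30):

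- f = 0.20: √(0.32/30) = 0.10
- f = 0.30: √(0.42/30) = 0.12
- f = 0.40: √(0.48/30) = 0.13

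With persistent cases and no treatment effect, a baseline difference *d* appears at discharge as d(1 − p). For d = 0.12 and p = 0.30 this is 0.12 × 0.70 = 0.084. The direction is random.

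**6. What remains detectable.** For the assumed 40% v 20%, exact Fisher power at 30 per arm is 30% with no baseline malnutrition. It is 17% at f = 0.20 and 10% at f = 0.40 when everyone malnourished at the end is counted. Restricting to patients not malnourished at baseline (24 and 18 per arm) gives 24% and 16%. Power is low under either definition.

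**The case against.** **No sentence says that baseline cases are counted.** This stands. A reader might infer from aim II that patients malnourished at entry are recorded as incident cases, but the article does not say so. *Incidence* can mean new cases, and the Secondary outcomes section brings baseline SGA into the outcome through a change score. What remains is that a change in a graded assessment is not turned into a case definition, and that the two sections give different end points.

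**An article leaves the covariate model of an exploratory binary outcome to fuller documents.** This largely stands: the absence of an adjusted model is not in itself a fault. Fisher's test is also named only among initial tests to be used as appropriate, and the GEE could include SGA. But the article does state a baseline-adjustment rule, and its terms stop at continuous outcomes.

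**The size is assumed.** This stands in full. The article gives no baseline prevalence, new-case rate or recovery rate. If the intervention helped baseline cases recover, they would carry information and the attenuation would be smaller.

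**There is no bias towards an arm.** This stands. A reader might infer that pre-existing malnutrition biases the comparison in one arm's favour. Under 1:1 randomisation it does not: imbalance is random, and the unadjusted test remains valid. The loss is in precision and interpretability.

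**Conclusion.** The point holds as a low-severity matter of outcome wording and analysis choice. Aim II and the Secondary outcomes section describe the malnutrition outcome differently, and neither fixes how patients malnourished at baseline are handled. The group comparison stated for such an outcome does not use the baseline SGA that will be on file.

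The consequence is conditional. If end status is compared unadjusted, and baseline cases persist or recover equally, the risk difference is multiplied by (1 − f): a fall from 0.20 to between 0.16 and 0.12 over an assumed baseline prevalence of 20% to 40%. Chance imbalance at entry then adds noise. These figures are illustrations, not estimates for this trial. Nothing here touches the co-primary outcomes or the sample size, and low power limits what any version of this comparison can show.

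**What to change.** 1. Reconcile aim II with the Secondary outcomes section: one outcome, one end point (discharge or day 15, whichever is meant), and an explicit statement of how patients malnourished at baseline are handled.
2. Compare malnutrition at the final assessment between groups, stratified by baseline SGA category or adjusted for it by logistic regression. If nearly all baseline cases stay malnourished, a logistic model may be unstable through separation, and a stratified (Mantel–Haenszel) comparison is safer.
3. Report, as a supporting figure, new malnutrition among patients not malnourished at baseline.
4. If the unadjusted figure at discharge is also shown, call it a prevalence.

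The cost is a few lines of text, since SGA is already scheduled at baseline and discharge. The new-case figure uses fewer patients and says nothing about recovery, which is why it supports the adjusted all-patient comparison and does not replace it.
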